### Uniformity in acupuncture performance

To ensure the uniformity of fascial-point acupuncture, the coordinating center will designate qualified physicians to train physicians from other participating units and monitor the operation process to ensure qualified performance before the experiment.

### Outcome measures

Therapeutic evaluation will be carried out by the same team member who will be blinded to treatment allocation. The primary evaluation indicators in this study are the hand-spasm score and the duration of spasm relief. The modified Ashworth scale will be used to evaluate the spasm of the hand (mainly including the thumb and the other four fingers) before and after treatment. After the patients have been treated with acupuncture and spasticity relieved, the timing will be started to evaluate the duration of spasticity relieved (during this period, the patient should avoid mental tension, so as not to interfere with the test results).

The secondary evaluation indicators included using electromyography (EMG) to detect the activity of the affected limbs, limb function and activity of daily living evaluation. The modified Ashworth scale will be used to evaluate the degree of hand spasm on the affected side at baseline, 4 weeks after intervention and at 1, 2, 4 and 6 months of follow-up [22]. The modified Ashworth scale was divided into 0, 1, 1^+^, 2, 3 and 4 grades, and was quantified as 0, 1, 2, 3, and 4 and 5 points, respectively (Table 1). Surface EMG will be used to record the changes in surface EMG of the upper limbs on the affected side at baseline and 4 weeks after intervention [23]. The simplified Fugl-Meyer scale will be used to evaluate the upper-limb motor function on the affected side and the modified Barthel Index will be used to evaluate activities of daily living at baseline, 4 weeks after intervention and at 1, 2, 4 and 6 months of follow-up [24, 25]. All measurements will be recorded in the data center.

**Table 1 Tab1:** Modified Ashworth scale

Grade	Assessment standard	Score
0	No increase in muscle tension	0
1	Muscle tension is increased slightly. When the affected part is passively flexed and stretched, it suddenly becomes stuck at the end of joint activity and then presents minimum resistance or release	1
1^+^	Muscle tension is increased slightly. Suddenly stuck in passive flexion and extension occurs within the last 50% of the range of ROM, and then shows minimal resistance	2
2	Muscle tension is increased significantly. Muscle tension of the affected limbs in passive motion increases significantly in most ROM ranges, but still easy to move	3
3	Muscle tension is increased severely. The affected limb’s passive movement has resistance over the whole ROM, so it is difficult to move	4
4	The affected part is rigid and inactive	5

*ROM* range of movement

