**Methods/design:**

This multicenter randomized controlled trial will compare the efficacy of fascial-point acupuncture versus sham acupuncture and routine rehabilitation therapy in stroke patients with hand spasm. Patients will be randomized to undergo either the fascial-point acupuncture, the sham acupuncture or the control (routine rehabilitation therapy). We will recruit 210 stroke inpatients who meet the trial criteria and observe the remission of hand spasm and improvement of limb function after 4 weeks of intervention. The first evaluation indices are the remission of hand spasm and the duration of spasm remission. The second evaluation indices are the hand function of the affected limbs and the activities of daily living. When the accumulative total number of cases included reaches 120, a mid-term analysis will be conducted to determine any evidence that experimental intervention does have an advantage.

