## Methods/design

### Trial design

This is a multicenter, prospective, randomized controlled trial supported by the Shanghai Science and Technology Commission. The trial will be carried out jointly by the Seventh People’s Hospital affiliated to Shanghai University of Traditional Chinese Medicine and two other hospitals in Shanghai. Patients meeting the pre-defined criteria will be randomly divided into three groups: an acupuncture group undergoing fascial-point acupuncture with routine rehabilitation treatment, a sham acupuncture group undergoing sham acupuncture near the fascial point with routine rehabilitation treatment, and a control group undergoing routine rehabilitation treatment. The patients will be followed up for 6 months to observe their hand spasm and limb function after treatment. The study flow chart is shown in Fig. 1. An example template for the content of admission plans, interventions and evaluation recommendations is shown in Fig. 2.

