### Sample size

Our study will be designed as a randomized controlled trial, and the main outcome is whether hand spasm after stroke is relieved after treatment. Current experience shows that the previous effectiveness rate of conventional acupuncture treatment is about 50%, and the expected effectiveness rate is 85%. The significance test level is 0.05, and the test power is 0.9. Sample size is calculated by using:

$$ \mathit{\mathsf{N}}={\left(\mathit{\mathsf{U}\mathsf{\alpha }}+\mathit{\mathsf{U}\mathsf{\beta }}\right)}^{\mathsf{2}}\times \mathsf{2P}\left(\mathsf{1}-\mathit{\mathsf{P}}\right)/{\left(\mathit{\mathsf{P}\mathsf{1}}-\mathit{\mathsf{P}\mathsf{0}}\right)}^{\mathsf{2}}, $$

where, *N* is the required sample size for each treatment group, and the sample size of each group is equal. When *α* is 0.05 and *β* is 0.1, the normal distribution quantile table shows that:
$$ \mathit{\mathsf{U}\mathsf{\alpha }}\left(\mathsf{0.05}\right)=\mathsf{1.65},\mathsf{and} $$
$$ \mathit{\mathsf{U}\mathsf{\beta }}\left(\mathsf{0.1}\right)=\mathsf{1.28}. $$

*P0* and *P1* represent the original curative effect and the expected curative effect, 50% and 85%, respectively. By substituting the above parameters and values into the formulas, 63 cases will be needed for each group. Accounting for a 10% expulsion rate, the final estimated sample size will be about 70 cases per group (210 in total).

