### Randomization

After signing the informed consent, participants will be randomly divided into three groups: an acupuncture group, a sham acupuncture group and a control group. Randomization will be accomplished by qualified researchers using randomization software to generate random-number sequences. In the process of randomization, allocation should be kept hidden. All patients will be randomly divided into groups in a ratio of 1:1:1. The strips revealing treatment allocation will be placed in sealed opaque envelopes with sequential numbers. After obtaining informed consent, the envelopes will be opened in turn. Patients and data analysts are not clear about the randomized grouping.

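### Duration of spasm relief is a primary indicator for all three arms, but its clock starts only after acupuncture and only once spasm is relieved

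*Protocol article*

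**What the plan says.** All places are in the protocol article.

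- **Status of the outcome.** Outcome measures: "The primary evaluation indicators in this study are the hand-spasm score and the duration of spasm relief". The Abstract (Methods/design) agrees: "The first evaluation indices are the remission of hand spasm and the duration of spasm remission". Neither limits duration to certain arms.
- **Timing rule.** Outcome measures: "After the patients have been treated with acupuncture and spasticity relieved, the timing will be started to evaluate the duration of spasticity relieved". This is the only rule given for when timing begins.
- **Arms.** Trial design describes, besides the fascial-point acupuncture group, "a sham acupuncture group undergoing sham acupuncture near the fascial point with routine rehabilitation treatment" and "a control group undergoing routine rehabilitation treatment". The Intervention section gives the control group positioning, exercises and exercise therapy, with no needling. Randomization: "All patients will be randomly divided into groups in a ratio of 1:1:1".
- **Relief as an outcome.** Sample size: "the main outcome is whether hand spasm after stroke is relieved after treatment". That section attributes a rate of about 50% to conventional acupuncture and expects 85%. It arrives at 63 per group, or 70 after allowing for 10% loss.

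**The concern.** The timing rule sets two conditions, and each sits badly with a primary indicator for three randomized arms.

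The first is needling. A control patient never meets it as written, so one third of the randomized patients could end the trial without a value. Timings not taken during the trial cannot be recovered at the analysis stage, and Trial status reports that recruitment is already under way.

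The second is relief. Relief is what the treatment is meant to produce, and the Sample size section treats it as the main outcome. A clock that starts only in relieved patients gives a value only to those who responded. If the analysis then uses only those values, the groups compared are no longer the randomized ones: the arm with the higher relief rate includes patients who would not have been relieved in the other arm. A difference in duration between such groups can reflect who was timed and not what the treatment did.

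**Working it through.** **1. The plan's own figure.** No figure is stated for duration. The 63 per group belongs to binary relief. The printed formula, taking P as the mean of 0.50 and 0.85 (0.675), gives (1.65 + 1.28)² × 2 × 0.675 × 0.325 / 0.35² = 8.585 × 0.43875 / 0.1225 = 30.7, so 31 and not 63. The loss step does reproduce: 63 / 0.9 = 70. The mismatch is a separate matter. Here 63 and 70 serve only as planned numbers per arm.

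**2. Who gets a start time under each reading.**

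| Reading of *acupuncture* in the timing rule | Acupuncture arm | Sham arm | Control arm |
|---|---|---|---|
| Strict: real needling at the fascial point | relieved patients | none | none |
| Any needling, sham included | relieved patients | relieved patients | none |
| Loose: study treatment | relieved patients | relieved patients | relieved patients |

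No reading gives every randomized patient a start time. The relief condition operates in all of them.

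**3. How many would be timed.** Assume relief of 85% with acupuncture and 50% with sham. The article gives the 50% for conventional acupuncture and states no sham or control rate.

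- Of 63 per arm: 63 × 0.85 = 53.6 and 63 × 0.50 = 31.5, so about 54 and 32. About 9 and 31 are untimed.
- Of 70 per arm: 59.5 and 35.
- Control: 0 on the first two readings; not calculable on the third.

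**4. What selection could do if only timed patients are compared.** Let ease of relief X be standard normal. Relief occurs when X exceeds −1.036 (85%) or 0 (50%). Let duration D have SD 1 and correlation ρ with X, with no treatment effect on D.

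- Mean of X in the relieved: 0.233 / 0.85 = 0.274 (acupuncture) and 0.798 (sham).
- Responder-only difference in D, acupuncture minus sham: ρ × (0.274 − 0.798) = −0.524ρ.
- Variance of D in the relieved: 1 − 0.359ρ² and 1 − 0.637ρ². At ρ = 0.5 these are 0.910 and 0.841, a pooled SD of 0.936.
- Standard error: 0.936 × √(1/53.55 + 1/31.5) = 0.936 × 0.2245 = 0.210.
- Chance of a two-sided 5% result against acupuncture: Φ(−1.96 + 0.261 / 0.210), about 24%.

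| ρ (assumed) | Responder-only difference (SD) | Chance of a significant result against acupuncture |
|---|---|---|
| 0 | 0 | 2.5% (nominal) |
| 0.3 | −0.16 | 11% |
| 0.5 | −0.26 | 24% |
| 0.7 | −0.37 | 47% |

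A negative ρ would turn the bias in favour of acupuncture.

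**5. An extreme case with a real effect.** Suppose relief and duration are the same normal variable, shifted by 1.036 between arms. Responders only: 1.311 − 0.798 = 0.513. With zeros for the unrelieved: 1.114 − 0.399 = 0.715. The responder-only difference is 1 − 0.513 / 0.715 = 28% smaller than that of the zero-scored endpoint.

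**The case against.** **Loose wording.** *Acupuncture* may stand for *treatment*. The Harms section has any event between consent and the start of the study intervention reported as unrelated to acupuncture, although enrolled subjects include controls. The sentence just before the timing rule assesses spasm before and after treatment in general. This stands as a real possibility. A reader might infer that the endpoint certainly does not exist in the control arm; the text supports that only on the literal reading. A strict reading would also put the sham arm in doubt, so strictness towards control and looseness towards sham need a reason.

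**Unrelieved patients.** A reader might infer that they are excluded from the analysis. The article does not say so. It says when timing starts, and a full protocol or analysis plan could score no relief as zero. This stands, which is why the responder-subset point is conditional. But no scoring rule can supply timings for relieved control patients that were never taken.

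**Size of bias.** A reader might infer that the 50% is the protocol's sham rate, that the effect would be about halved, or that a real effect would be reversed. The 50% is for conventional acupuncture. *About half* compares 0.513 with the latent shift of 1.036, which is not an endpoint; against the zero-scored endpoint the loss is 28%, and only if relief and duration are one variable. In that model the responder mean rises with the treatment effect, so reversal cannot occur. The deficits in the no-effect illustration arise only through a correlation that the article does not give.

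**The other primary indicator.** The modified Ashworth score is scheduled in all arms, and the trial is sized on relief. This stands and lowers the severity.

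**Conclusion.** The concern holds and should be fixed, but it is not fatal. The article states a measurement rule for a primary indicator that, followed as written, gives the control arm (and arguably the sham arm) no start time. On any reading, the rule makes the start depend on relief, a post-randomization outcome expected to differ between arms. That conclusion rests on the wording alone.

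The numbers rest on assumptions. About 54 and 32 timed patients of 63 requires a 50% relief rate in the sham arm. The bias figures require that unrelieved patients have no value in the analysis and that ease of relief and duration are correlated; with no correlation there is no selection bias.

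It would go too far to say that the trial cannot answer its three-arm question. The other primary indicator is measured in every arm, and the article does not say that both indicators must succeed.

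**What to change.** Rewrite the timing rule so that duration exists for every randomized patient:

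- Start the clock at the end of the same pre-stated session in all three arms; in control, at the end of the routine rehabilitation session.
- Score 0 for any patient whose modified Ashworth score has not fallen.
- Compare all randomized patients with a rank-based or time-to-return method.

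If control patients cannot be timed, declare duration a secondary outcome for acupuncture versus sham only, still with 0 for no relief.

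The cost is a change to the protocol and case report form, plus timed observation of control patients. The burden of that observation cannot be judged from the article, which gives no expected length of relief. The zeros form a spike, which a rank method can handle. The zero-scored outcome also overlaps with relief: if relieved patients in both arms had the same duration L, the means would be 0.85L and 0.50L under the assumed rates, a difference due to the relief rates alone. Reporting the relief rate beside it would make the overlap visible. Because recruitment is under way, the change is worth making promptly, with a note of which patients were timed under the present rule.

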### Harms

In our study, an adverse event will be defined as any untoward medical occurrence in a subject without regard to the possibility of a causal relationship. Adverse events will be collected after the subject has provided consent and enrolled in the study. If a subject experiences an adverse event after the informed consent document has been signed (entry) but the subject has not started to receive the study intervention, the event will be reported as not related to acupuncture. All adverse events occurring after entry into the study and until hospital discharge will be recorded. An adverse event that meets the criteria for a serious adverse event (SAE) between study enrollment and hospital discharge will be reported to the local Institutional Review Board.

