### Intervention

The interventions in the three groups are as follows:
Acupuncture group

In addition to routine rehabilitation treatment, fascial-point acupuncture will be given five times a week for 4 weeks, with 30 min each time.

Location of fascial points: the patient will be in a sitting or supine position and the physician will be placed on the affected side. First, 75% alcohol cotton ball will be used to disinfect the patients´ dorsal between the first metacarpal bone and the second metacarpal bone and the thumb of the operator. Then, the operator will apply one-way pressure with thumb on the dorsal between the first metacarpal bone and the second metacarpal bone from the distal end to the closel end. During this process, the most obvious pain point or a cord nodule can be touched can be touched, which is the fascial point as shown in Fig. 3.

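### Adverse event recording and SAE reporting stop at hospital discharge, a point that is not fixed in study time and leaves events after discharge uncaptured, although patients are assessed up to 6 months

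*Protocol article*

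**What the plan says.** The Harms section begins collection at consent and enrollment and ends it at discharge: "All adverse events occurring after entry into the study and until hospital discharge will be recorded". For SAEs it gives the same interval; those occurring "between study enrollment and hospital discharge will be reported to the local Institutional Review Board". An adverse event is defined there without any requirement of a causal link to treatment.

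The rest of the design runs on a different clock. Under Intervention, "fascial-point acupuncture will be given five times a week for 4 weeks"; the sham sessions and the routine rehabilitation follow the same weekly frequency and duration. Under Trial design, "The patients will be followed up for 6 months to observe their hand spasm and limb function after treatment". Outcome measures schedules the modified Ashworth, Fugl-Meyer and Barthel assessments at baseline, at 4 weeks and at 1, 2, 4 and 6 months of follow-up. The Abstract describes the participants as inpatients, and Study setting places treatment in the recruiting hospitals. The article gives no length of stay, no discharge criterion and no requirement to remain in hospital for the course.

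**The concern.** The end of safety recording is an administrative event that differs from patient to patient and happens after randomization. It is neither a study day nor a study visit. Three consequences need to be kept apart.

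- **Follow for any patient discharged before the 6-month assessment:** events after discharge fall outside the recording window, even when the patient returns for a scheduled assessment. Such events would meet the article's own definition of an adverse event.
- **Would follow if discharge came before week 4:** events in the remaining part of the treatment course would also be lost.
- **Would follow if length of stay differed by arm:** the arms would be observed for harms over different lengths of time, and crude proportions of patients with an event would not be comparable.

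At stake is the completeness of the safety data and how far they can be compared across arms. The efficacy outcomes and the sample size are not affected.

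**Working it through.** The plan gives no figure on this point to reproduce. The check sets the windows side by side and then sizes the gap.

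**Windows stated in the article**

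| Element | Start | End | Section |
|---|---|---|---|
| Adverse event recording | study entry | hospital discharge | Harms |
| SAE reporting to the review board | enrollment | hospital discharge | Harms |
| Treatment | start of course | 4 weeks, 5 sessions a week | Intervention |
| Efficacy assessment | baseline | 6 months of follow-up | Trial design; Outcome measures |

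Only the first two rows end at a point that is not fixed in study time. No other section extends them or equates discharge with the end of treatment.

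**Sessions:** 5 × 4 = 20.

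**Share of calendar study time covered.** Six months is 6 × 365.25 / 12 = 182.6 days. If follow-up starts after the course, study time is 28 + 182.6 = 210.6 days. If the 6 months run from entry, it is 182.6 days. Day of discharge is not in the documents; days 14 to 56 are an assumed range.

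- Share of study time = day of discharge / study time
- Share of course = min(day of discharge, 28) / 28

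| Assumed discharge | Share of 210.6 days | Share of 182.6 days | Share of 28-day course |
|---|---|---|---|
| Day 14 | 6.6% | 7.7% | 50% |
| Day 21 | 10.0% | 11.5% | 75% |
| Day 28 | 13.3% | 15.3% | 100% |
| Day 42 | 19.9% | 23.0% | 100% |
| Day 56 | 26.6% | 30.7% | 100% |

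In weeks, for discharge at the end of the course: 4 / (4 + 26) = 13%.

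**What unequal windows could do.** With a constant event rate per 28 days, identical for everyone, the expected proportion of patients with a recorded event is 1 − exp(−rate × days / 28). Rates and windows are assumptions.

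| Assumed rate per 28 days | 21-day window | 28-day window | 42-day window |
|---|---|---|---|
| 0.05 | 3.7% | 4.9% | 7.2% |
| 0.10 | 7.2% | 9.5% | 13.9% |
| 0.20 | 13.9% | 18.1% | 25.9% |

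For example, at rate 0.10 and 42 days: 1 − exp(−0.15) = 13.9%. At a common true rate, the recorded proportion moves with the window alone. This shows what would happen if stays differed between arms; it is not evidence that they do.

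**The case against.** The best defence is that these are inpatients treated in the recruiting hospitals, so a window that ends at discharge may well contain the whole needling course. The needling-related problems that the article mentions, such as bleeding at the needle hole, pain and fainting, arise at the session. The rule is the same for all arms, nothing in the article contradicts it, and no comparison of safety between arms is announced that it would invalidate.

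Much of this stands, and it rules out several stronger readings that a reader might infer:

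- **That harms during treatment are being lost.** This needs discharge before week 4, which the article neither states nor excludes. Even then, a patient discharged early still contributes every event up to discharge; only later ones are lost.
- **That the arms are observed unequally.** The article gives no discharge criteria and no length of stay by arm. Stays that merely vary between patients do not bias a randomized comparison unless their distribution differs by arm. A difference is conceivable, since discharge follows randomization and staff can see who receives no needling, but it is not shown.
- **That 87% of the risk goes unobserved.** The 13% is a share of calendar time. Most of the denominator is follow-up without study needling, and with discharge at week 4 all 20 sessions are covered.
- **That a planned benefit-harm conclusion is one-sided.** The stated objectives and outcomes concern spasm, function and daily living; the article plans no benefit-harm analysis.

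The defence does not remove the central point. If harms arise mainly at the session, that argues for a window guaranteed to contain all sessions, and discharge gives no such guarantee. It also gives no reason to leave events, including serious ones, unrecorded when patients are assessed anyway. Nor can the point be put down to condensation in an article: the end point is stated explicitly.

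**Conclusion.** The concern holds in a limited form. Adverse event recording and SAE reporting end at a patient-specific event after randomization that is tied neither to the course nor to the follow-up schedule, so events after discharge are not captured. With discharge at week 4, about 13% of calendar study time is covered (15% if the 6 months run from entry), along with the full set of 20 sessions. Over the assumed discharge range of day 14 to day 56, coverage is 6.6% to 26.6% of 210.6 days.

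Missed events within the course and non-comparable proportions between arms remain conditional on lengths of stay that the documents do not give. This is a weakness in a stated design choice and not an internal contradiction. It is worth correcting because the correction is cheap.

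**What to change.** Replace the end point in the Harms section as follows:

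1. In all three arms, record adverse events and SAEs from consent to a fixed study point no earlier than the 4-week assessment, whether or not the patient has been discharged.
2. Ask about adverse events and SAEs at the existing 1-, 2-, 4- and 6-month assessments.
3. Report SAEs to the review board over that same period.
4. Summarize events by arm over the common 4-week window and show later events separately, so that the comparison between arms does not depend on length of stay.

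The cost is a short adverse event entry in the case report form at assessments already planned, plus SAE reports over a longer period. No new visits and no change in sample size are needed.
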